### **7.8.1 Analysis of Primary Efficacy Endpoint**

The primary efficacy endpoint analysis is the baseline-adjusted change in cT1 as assessed by LMS at 17-19 weeks in subjects treated with placebo as compared to subjects treated with GR-MD-02 (8 mg/kg/week). Change in cT1 as assessed by LMS from baseline will be

compared between treatments groups using analysis of covariance (ANCOVA) adjusted for baseline cT1 as assessed by LMS. Treatment group will be included in the model as indicator variables where T1 = 1 if subject is randomly assigned to GR-MD-02 and 0 otherwise. The following hypothesis will be tested based on the parameter estimates (and standard errors) from the fit of the ANCOVA model:

H01:  $\Delta T1 - \Delta P = 0$  vs. HA1:  $\Delta T1 - \Delta P \neq 0$

### **7.8.2 Analysis of Key Secondary Efficacy Endpoints**

Key secondary endpoints will be examined using a gatekeeper statistical approach. If the primary endpoint is significant ( $\alpha < 0.05$ ), analysis will proceed to the secondary endpoints. Since the evaluation of secondary endpoints will proceed using a pre-specified hierarchy without statistical correction for multiplicity, if a secondary endpoint does not meet statistical significance, all subsequent analysis will be treated as exploratory only.

### **7.8.3 Analysis of the Exploratory Efficacy Endpoint**

Exploratory endpoints will be analyzed in the same fashion as the primary endpoint.

### **7.8.4 Safety Analyses**

All subjects receiving any part of at least 1 infusion of study treatment will be evaluated for safety. The safety analyses will include evaluation of the incidence of treatment-emergent adverse events (TEAEs), Grade 3 or greater AEs, SAEs and AEs leading to discontinuation of study treatment using the Common Terminology Criteria for Adverse Events Version 4.0 or higher. Laboratory and vital signs assessments will be evaluated over time on study using descriptive statistics. Shift analyses of relevant clinical laboratory parameters will be produced showing shifts across low, normal, and high categories.

All heart rate (bpm), 12-lead ECG parameters, PR Interval (msec), QRS Interval (msec), QT Interval (msec), and QTc Interval (msec) will be measured, and overall interpretation will be summarized for all subjects by study visit including the last visit of the study.

Electrocardiogram parameters will be summarized using descriptive statistics. Mean and mean change from baseline values will be presented for every scheduled assessment. Change

from baseline will be calculated as the post-baseline measurement minus the baseline measurement. If either the baseline or post-baseline value is missing, the observation will not be included in the change from baseline summary. In addition, counts and percentages for ECG overall interpretation (normal, abnormal, clinically significant, and not clinically significant) will be presented for each scheduled assessment.

For physical examinations, the results (normal, abnormal, or not done) by body system of the full physical examination at the randomization visit and follow-up visits will be summarized with descriptive statistics by treatment group and visit. For physical examinations performed at postrandomization time points, the number and percent of subjects with no change or any significant changes since the previous examination will be presented by treatment received. In addition, a shift table will be included to summarize the number and percent of subjects with changes from baseline to each postrandomization visit by body system for each treatment group. The number and percent of subjects with normal and abnormal results (clinically significant vs. not clinically significant) for each body system will be presented by treatment group.

Vital sign measurements (respiration, heart rate, temperature, systolic and diastolic blood pressure), height (at screening only), and BMI will be summarized descriptively at each scheduled visit. Mean and mean change from baseline values will be presented. Change from baseline will be calculated as post-baseline measurement minus baseline measurement. If either the baseline or post-baseline value is missing, the observation will not be included in the change from baseline summary.

All safety data will be listed by subject, parameter, and time point.

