#### **4.1.2 Exclusion Criteria**

Subjects meeting any of the following criteria will be excluded from the study:

1. A history of hepatic decompensation including any episode of variceal bleeding, clinically detectable ascites, or overt hepatic encephalopathy.
2. Status post TIPS (Transjugular Intrahepatic Porto-systemic Shunt) procedure.
3. Evidence of other forms of chronic liver disease including viral hepatitis B or C, primary biliary cirrhosis, primary sclerosing cholangitis, Wilson's disease, alpha-1 antitrypsin deficiency, alcoholic hepatitis, hemochromatosis, liver cancer, or history of biliary diversion.
4. Any of the following laboratory values:
  - a. Serum alanine aminotransferase (ALT) and aspartate aminotransferase levels  $> 10X$  upper limits of normal
  - b. Serum creatinine  $\geq 2.0$  mg/dL
  - c. Platelet count  $< 60,000/mm^3$
  - d. Serum albumin  $\leq 2.8$  g/dL
  - e. INR  $\geq 1.7$
  - f. Direct bilirubin  $\geq 2.0$  mg/dL
5. A MELD score  $\geq 15$  or Child-Pugh-Turcotte Stage B or C.
6. Known positivity for Human Immunodeficiency Virus (HIV) infection.
7. Any patient who had major surgery within 8 weeks of Day 1, significant traumatic injury, or anticipation of need for major surgical procedure during the course of the study.

8. Weight reduction surgery within the past 3 years.
9. Any subject with current, significant alcohol consumption or a history of significant alcohol consumption for a period of more than 3 consecutive months any time within 1 year prior to screening will be excluded. Significant alcohol consumption is defined as more than 20 grams per day in females and more than 30 grams per day in males. On average, a standard drink in the US is considered to be 14 grams of alcohol equivalent to 12 fluid oz of regular beer (5% alcohol), 5 fluid oz of table wine (12% alcohol), or 1.5 fluid oz of 80 proof spirits (40% alcohol).
10. Any subject who has clinically significant and uncontrolled cardiovascular disease (e.g., uncontrolled hypertension, myocardial infarction, unstable angina), New York Heart Association (NYHA) Grade II or greater congestive heart failure, serious cardiac arrhythmia requiring medication, or Grade II or greater peripheral vascular disease within 12 months prior to Day 1.
11. Any subject with concurrent infection including diagnoses of fever of unknown origin (FUO) (subjects must be afebrile at the start of therapy).

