### **6.3.4 Adverse Events**

#### **6.3.4.1 Definitions of Adverse Events**

The investigator is responsible for reporting all treatment-emergent AEs (TEAEs) that are observed or reported during the study, regardless of their relationship to IMP or their clinical significance.

An AE is defined as any untoward medical occurrence in a subject enrolled into this study regardless of its causal relationship to IMP. Subjects will be instructed to contact the investigator at any time after randomization if any symptoms develop.

A TEAE is defined as any event not present before exposure to IMP or any event already present that worsens in either intensity or frequency after exposure to IMP.

An SAE is defined as any event that results in death, is immediately life threatening, requires inpatient hospitalization or prolongation of existing hospitalization, results in persistent or significant disability/incapacity, or is a congenital anomaly/birth defect. Important medical events that may not result in death, be life threatening, or require hospitalization may be considered SAEs when, based upon appropriate medical judgment, they may jeopardize the subject or may require medical or surgical intervention to prevent one of the outcomes listed in this definition. Examples of such medical events include allergic bronchospasm requiring intensive treatment in an emergency room or at home, blood dyscrasias or convulsions that do not result in inpatient hospitalization, or the development of drug dependency or drug abuse.

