#### **6.3.4.2 Eliciting and Documenting Adverse Events**

All AEs (serious and non-serious) will be assessed beginning at screening and up to 42 days after the last dose of IMP.

Serious AEs that occur more than 42 days after the last dose of IMP need not be reported unless the investigator considers them related to IMP.

At every study visit, subjects will be asked a standard nonleading question to elicit any medically related changes in their well-being. They will also be asked if they have been hospitalized, had any accidents, used any new medications, or changed concomitant medication regimens (both prescription and OTC medications).

In addition to subject observations, AEs identified from any study data (e.g., laboratory values, physical examination findings, ECG changes) or identified from review of other documents that are relevant to subject safety will be documented on the AE page in the CRF.

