### **6.3.4.3 Reporting Adverse Events**

All AEs reported or observed during the study will be recorded on the AE page in the CRF. Information to be collected includes drug treatment, dose, event term, time of onset, investigator-specified assessment of severity and relationship to IMP, time of resolution of the event, seriousness, any required treatment or evaluations, and outcome. Adverse events resulting from concurrent illnesses, reactions to concurrent illnesses, reactions to concurrent medications, or progression of disease states must also be reported. All AEs will be followed to adequate resolution. The Medical Dictionary for Regulatory Activities (MedDRA, Version 17.1) will be used to code all AEs.

Any medical condition that is present at the time that the subject is screened but does not deteriorate should not be reported as an AE. However, if it deteriorates at any time during the study, it should be recorded as an AE.

Any AE that meets SAE criteria (Section 6.3.4.1) must be reported to the sponsor (designee) immediately (i.e., within 24 hours) after the time study center personnel first learn about the event.

Study personnel should complete the AE CRF, designating the event as serious.

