### **6.3.6 Laboratory Analyses**

Any abnormal laboratory test results (hematology, clinical chemistry, or urinalysis) or other safety assessments (eg, ECGs, radiological scans, vital sign measurements), including those that worsen from baseline, believed to be clinically significant in the medical and scientific judgment of the investigator are to be recorded as AEs or SAEs.

However, any clinically significant laboratory assessments that are associated with the underlying disease, unless judged by the investigator to be more severe than expected for the subject's condition, are not to be reported as AEs or SAEs.

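### The low/normal/high laboratory shift table cannot count a further rise in ALT or AST in subjects who enter above the upper limit of normal

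*Protocol*

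**What the plan says.** Section 7.8.4 of the Protocol sets the laboratory shift analysis: "Shift analyses of relevant clinical laboratory parameters will be produced showing shifts across low, normal, and high categories". The synopsis repeats this under Safety Assessments and under Statistical Methods. Apart from the shift table, 7.8.4 plans only descriptive statistics over time for laboratory values. Mean change from baseline is specified there for ECG and vital signs but not for laboratory values.

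Exclusion 4a in Section 4.1.2 concerns "Serum alanine aminotransferase (ALT) and aspartate aminotransferase levels" and applies only above 10 times ULN. ALT and AST are in the chemistry panel (6.3.8), drawn at screening and before dosing at Visits 1, 5 and 9.

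Three other provisions bear on laboratory worsening:

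- Section 6.3.6 makes abnormal results adverse events, "including those that worsen from baseline, believed to be clinically significant in the medical and scientific judgment of the investigator". It then exempts "any clinically significant laboratory assessments that are associated with the underlying disease, unless judged by the investigator to be more severe than expected".
- Section 7.8.4 counts Grade 3 or greater adverse events "using the Common Terminology Criteria for Adverse Events Version 4.0 or higher". It does not apply those grades to the laboratory values themselves.
- Section 7.8.4 also has all safety data listed subject by subject, and Section 7.8 includes the maximum in the summaries of continuous variables.

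**The concern.** Subjects have biopsy-proven NASH with stage 3 fibrosis, and the entry rule plainly foresees raised aminotransferases. For anyone who starts above ULN, the highest category is already occupied, so a further rise has no cell to go to. Laboratory abnormalities are a stated safety endpoint (7.4), and the shift table is the only laboratory analysis in the protocol that expressly ties a subject's on-treatment value to that subject's own baseline. A drug-related rise in liver enzymes in these subjects would leave the table unchanged, and a reader comparing the arms on it would see no worsening.

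**Working it through.** **Inputs.** Three shift categories (7.8.4); ALT/AST admitted up to 10 times ULN (4.1.2, exclusion 4a); about 30 subjects at 1:1, so about 15 per arm (7.5); scheduled chemistry after the first dose at Visits 5 and 9 (6.1.2.3). The baseline ALT/AST distribution is not given. ALT and AST are not named as the relevant parameters in 7.8.4; their inclusion is inferred from the panel and the indication.

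**The plan's own figure.** The 15 per arm reproduces. The normal approximation gives 2 x (1.960 + 0.842)^2 x (42.5/45.1)^2 = 13.9, so 14 per arm. Exact t-test power at 15 per arm is 80.1%, and 80.0% with the synopsis pair of 53 and 50 ms. Nothing below depends on this beyond the 15.

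**Step 1: cells open to a rise, by baseline row.**

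| Baseline | Possible cells | Cells that record a rise |
|---|---|---|
| Low | 3 | 2 |
| Normal | 3 | 1 |
| High | 3 | 0 |

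**Step 2: example values in multiples of ULN (assumed).**

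| Baseline to on-treatment | Fold rise | Table entry | Counted as a rise? |
|---|---|---|---|
| 0.8 to 1.5 | 1.9 | normal to high | yes |
| 1.5 to 3 | 2.0 | high to high | no |
| 1.5 to 8 | 5.3 | high to high | no |
| 2 to 8 | 4.0 | high to high | no |
| 3 to 9 | 3.0 | high to high | no |
| 10 to 30 | 3.0 | high to high | no |

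The smallest rise in the list is the only one counted.

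**Step 3: subjects per arm who can register a rise.** This is 15 - k, where k is the number above ULN at baseline:

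- k = 0: 15 (nothing lost)
- k = 5: 10
- k = 10: 5
- k = 15: 0

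**Step 4: effect on the count (assumed subjects).** If one subject in an arm goes from 2 to 8 times ULN, the planned table counts 0/15 worsened, and a table by multiple of own baseline counts 1/15 = 6.7%. With two such subjects the counts are 0/15 and 2/15 = 13.3%.

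**Step 5: recovery from the listings.** 15 subjects x 2 scheduled draws gives at most 30 values after the first dose per analyte per arm, so a reader could make the count by hand.

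**The case against.** The strongest reply is that shift-table banding belongs in the SAP. Section 7 calls itself a summary, and 7.8.4 does not say that the low/normal/high display is the only one. A SAP that added graded or own-baseline tables would comply with it. That is so, and the SAP is not at hand. The point therefore concerns only the categories that the protocol itself fixes, in three places, and those do not suit these analytes in this population.

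The second reply is that worsening is caught elsewhere. A treatment-emergent event includes "any event already present that worsens in either intensity or frequency after exposure to IMP" (6.3.4.1), and Section 6.3.4.3 says of a condition present at screening that "if it deteriorates at any time during the study, it should be recorded as an AE". Clinically significant biochemical change from baseline is a ground for withdrawal (4.2.1), and every value is listed. This stands as far as it goes: a rise is not lost from the trial. None of these routes is a systematic count by arm of measured worsening, however:

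- The adverse event route depends on investigator judgement, and the disease-associated exemption in 6.3.6 is most likely to reach aminotransferases in NASH. A large rise could still be reported as more severe than expected.
- The Grade 3 count applies to reported events. Section 6.3.4.4 has investigators rate severity by effect on daily activities, so a rise without symptoms could be rated mild whatever its size.
- Withdrawal is discretionary.
- A visit maximum does not show change from that subject's own baseline.
- Listings give no count unless someone makes one.

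The third reply, that the size is unknown and the examples are invented, is accepted. The structural gap in the table does not depend on them.

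**Conclusion.** The concern holds. For a subject who enters above ULN, the planned shift table has no cell that records a rise in ALT or AST. This follows from the stated categories and the entry limit alone. How many subjects it affects cannot be known from the protocol: anywhere from none to all of about 15 per arm. The practical effect is minor. Some 30 subjects are fully listed, other routes can show a rise, and no sample size, efficacy conclusion or decision rule changes. The change should be made because the table misses what it is most needed for in a liver trial and correcting it costs very little.

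**What to change.** In Section 7.8.4 and at both places in the synopsis, replace the low/normal/high shift for ALT and AST with:

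1. A baseline-to-worst-on-treatment shift by CTCAE grade (7.8.4 already names version 4.0 or higher) or by multiple of ULN, for example up to 1, above 1 to 3, above 3 to 5, above 5 to 10, and above 10.
2. The number and percent of subjects per arm by worst multiple of their own baseline. This is needed as well because bands can hide a rise within a band: 1.5 to 3 times ULN is a doubling that stays in the second band.

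The same treatment can reasonably extend to alkaline phosphatase and GGT, for which 4.1.2 sets no entry limit, and to bilirubin, where direct bilirubin below 2.0 mg/dL is admitted. The protocol does not say whether these will be raised at baseline. Keep low/normal/high for the other analytes.

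The cost is one amended sentence where it appears and one or two extra tables from chemistry already drawn at screening and Visits 1, 5 and 9. No new samples or visits are needed. A protocol amendment needs ethics board approval (10.2.1), so the wording could travel with another amendment. Because 7.8.4 does not rule out further displays, the tables could be specified in the SAP meanwhile.

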### **7.8.5 Other Analyses**

Summary statistical analyses will be provided for baseline assessments such as demographics and medical history.

The numbers and percentages of subjects in each treatment group taking concomitant medications, defined as non-study medications with a stop date on or after the date of the first infusion of study medication, will be summarized by dictionary coded terms (World Health Organization Drug Dictionary (Version 1 Sep 2014)). Medications that started prior to the first infusion of study medication but continued during treatment will also be defined as

concomitant. Ongoing medications without stop dates are considered concomitant. Prior medications, defined as nonstudy medications with a stop date before the first infusion of study medication, will also be summarized by treatment group. Medications with partial onset/stop dates that indicate that the medication could be concomitant in relation to the start date of study medication will be classified as concomitant. Otherwise, they will be classified as prior medications.

Investigational medicinal product exposure and overall percent compliance will be calculated per subject in the FAS population and summarized by treatment group using descriptive statistics.

### **7.8.6 Interim Analyses**

There is no planned interim analysis.

## **7.9 Data Quality Assurance**

The sponsor's (or an authorized representative's) Quality Assurance department may conduct on-site audits of all aspects of the clinical study either during the study or after the study has been completed.

The clinical study may also be subject to inspection by regulatory authorities (national or foreign) as well as the IECs/IRBs to ascertain that the study is being or has been conducted in accordance with protocol requirements, GCPs, as well as the applicable regulatory requirements.

### **7.9.1 Data Management**

As part of the responsibilities assumed by participating in the study, the investigator agrees to maintain adequate case histories for the subjects treated as part of the research under this protocol. The investigator agrees to maintain accurate CRFs and source documentation as part of the case histories. These source documents may include hospital records, clinical and office charts, chest x-ray and interpretation, questionnaires, pharmacy dispensing and other records, etc.

Clinical data management will be performed in accordance with applicable Galectin Therapeutics standards and data cleaning procedures to ensure the integrity of the data, e.g., removing errors and inconsistencies in the data. Adverse events and concomitant medication terms will be coded using the MedDRA, an internal validated medication dictionary.

## **8 Ethics**

### **8.1 Independent Ethics Committee or Institutional Review Board**

Federal regulations and the International Conference on Harmonisation (ICH) guidelines require that approval be obtained from an Institutional Review Board (IRB)/ Independent Ethics Committee (IEC) before participation of human subjects in research studies. Before study onset, the protocol, informed consent, advertisements to be used for the recruitment of study subjects, and any other written information regarding this study to be provided to the subject or the subject's legal guardian must be approved by the IRB/IEC. Documentation of all IRB/IEC approvals and of the IRB/IEC compliance with ICH harmonised tripartite guideline E6(R1): Good Clinical Practice (GCP) will be maintained by the study center and will be available for review by the sponsor or its designee.

All IRB/IEC approvals should be signed by the IRB/IEC chairman or designee and must identify the IRB/IEC name and address, the clinical protocol by title or protocol number or both, and the date approval or a favorable opinion was granted.

The investigator is responsible for providing written summaries of the progress and status of the study at intervals not exceeding 1 year or otherwise specified by the IRB/IEC. The investigator must promptly supply the sponsor or its designee, the IRB/IEC, and, where applicable, the institution, with written reports on any changes significantly affecting the conduct of the study or increasing the risk to subjects.

### **8.2 Ethical Conduct of the Study**

The study will be performed in accordance with the ethical principles that have their origin in the Declaration of Helsinki, ICH Good Clinical Practice, and all applicable regulations.

### **8.3 Subject Information and Consent**

A written informed consent in compliance with US Title 21 Code of Federal Regulations (CFR) Part 50 shall be obtained from each subject before entering the study or performing any unusual or non-routine procedure that involves risk to the subject. An informed consent template may be provided by the sponsor to investigative study centers. If any institution-specific modifications to study-related procedures are proposed or made by the study center,

the consent should be reviewed by the sponsor or its designee or both before IRB/IEC submission. Once reviewed, the consent will be submitted by the investigator to his or her IRB/IEC for review and approval before the start of the study. If the ICF is revised during the course of the study, all active participating subjects must sign the revised form.

Before recruitment and enrollment, each prospective subject or his or her legal guardian will be given a full explanation of the study and be allowed to read the approved ICF. Once the investigator is assured that the subject/legal guardian understands the implications of participating in the study, the subject/legal guardian will be asked to give consent to participate in the study by signing the ICF.

The investigator shall retain the signed original ICF(s) and give a copy of the signed original form to the subject or legal guardian.

